### Patient Population

2.2

Participation in the study may be offered to ICM patients requiring VT radiofrequency ablation, either during consultation (outpatient) or during hospitalization (for inpatients requiring urgent intervention). Participation in the study will be proposed and explained to the patient along with the provision of an information letter. Signed informed consent will be obtained before patients are randomized. Antithrombotic treatment will be adapted according to the randomization group. Randomization will be centralized through the Ennov software (Ennov Clinical, Groupe Ennov, Paris, France), generating blocks of variable size to ensure the unpredictability of treatment allocation. The block sizes and order of treatment within each block will be randomly generated. Randomization will be stratified by center.

Patients must meet the following criteria to be eligible for the study: (i) patients aged > 18 years, (ii) requiring first‐time radiofrequency ablation for VT associated with ICM, (iii) implanted with an ICD and monitored remotely through telemonitoring, (iv) for women of childbearing age, use of effective contraception until hospital discharge, (v) provision of written informed consent, and (vi) affiliated with a health insurance system or benefiting from such coverage.

Patients meeting any of the following criteria will be excluded from the study: (i) history of cardiac surgery compromising epicardial access (such as coronary artery bypass grafting, valve replacement, or other surgeries that may have caused pericardial adhesions), (ii) presence of a left ventricular thrombus detected on pre‐procedure imaging, (iii) use of anticoagulant therapy that cannot be temporarily discontinued, (iv) use of dual antiplatelet therapy that cannot be temporarily replaced by single antiplatelet therapy, (v) history of pericarditis, (vi) history of thoracic radiotherapy, (vii) contraindication to general anesthesia, (viii) pregnant or breastfeeding women, (ix) history of type 2 heparin‐induced thrombocytopenia (as heparin injection is required during the procedure), and (x) adults under legal protection (e.g., guardianship, curatorship), deprivation of liberty, or inability to provide informed consent.

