#### Endocardial Approach Only

2.3.2

Regarding antithrombotic management: (i) for patients on direct oral anticoagulants (DOACs), the morning dose (apixaban, dabigatran, or morning dose of rivaroxaban) or the evening dose (evening dose of rivaroxaban) will be withheld; (ii) for patients on vitamin K antagonists (VKAs), the procedure will be performed if the international normalized ratio (INR) is < 3 on the day before the procedure; and (iii) for patients on antiplatelet agents, the procedure will be performed regardless of the combination of antiplatelet therapy.

The defibrillator will be deactivated at the beginning of the procedure. Endocardial access to the left ventricle will be obtained via a retrograde aortic approach (through femoral arterial puncture) and/or a transseptal approach (through femoral venous puncture) according to the center's usual practice and the presumed location of the VT. A quadripolar catheter will be placed inside the right ventricle to pace the ventricle during the procedure if needed for VT induction/overdrive and to perform programmed ventricular stimulation at the end of the procedure.

Unfractionated heparin will be administered at the beginning of the procedure (100–120 IU/kg) and then regularly during the procedure to maintain an activated clotting time (ACT) of approximately 300 s.

The procedure will be performed using conventional 3D mapping techniques. A high‐density map during sinus rhythm or pacing will be created at the beginning of the procedure to identify low‐voltage areas and the presence of late potentials, abnormal ventricular electrograms, and deceleration zones. VT induction will be attempted if desired to perform an activation map. A complete substrate ablation strategy will be employed, supplemented by specific strategies for the ablation of induced VTs (pace mapping and entrainment mapping). Radiofrequency energy will be delivered using irrigated tip catheters at 30–50 W, preferably with isotonic saline, for a maximum duration of 60 s.

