#### Combined Endo‐Epicardial Approach

2.3.3

Regarding antithrombotic management: (i) for patients on DOACs, the last dose should be taken at least 3 days before the procedure (apixaban and rivaroxaban) or 4 days before (dabigatran); (ii) for patients on VKAs, therapy will be discontinued 5 days before the procedure, which can be performed if the INR is < 1.5 on the day before the procedure; (iii) for patients on antiplatelet agents, aspirin will be continued alone and any other antiplatelet agent will be halted at least 5 days before the procedure.

The defibrillator will be deactivated at the beginning of the procedure. A quadripolar catheter will be placed inside the right ventricle to pace the ventricle during the procedure if needed for VT induction/overdrive and to perform programmed ventricular stimulation at the end of the procedure.

The first step of the procedure will aim at obtaining pericardial access, which will be performed using a Tuohy needle. To minimize the risk of complications, an anterior approach will be preferred, using fluoroscopy in the lateral projection to avoid diaphragmatic puncture, and a long guidewire will be placed before advancing the sheath to confirm intrapericardial placement. Other specific techniques may be used according to the operator's preference (e.g., micropuncture, CO2 insufflation). A deflectable sheath will then be introduced into the pericardium, and a high‐density mapping of the epicardium in sinus rhythm/pacing will be performed to identify low‐voltage areas and search for the presence of late potentials, abnormal ventricular electrograms, and deceleration zones. The left phrenic nerve will be located by high‐output stimulation (10 mA), and its position annotated on the map.

After completing the epicardial map, before mapping the left ventricular endocardium, and in the absence of pericardial bleeding related to the puncture, unfractionated heparin will be administered (100–120 IU/kg) and then regularly during the procedure to maintain an ACT of approximately 300 s.

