#### Data Collection

2.5.1

The measurement time points for each assessed parameter are shown in Table 1. Descriptive data for the study population will be collected before the ablation procedure. These data will be presented using descriptive statistics.

**Table 1 jce16630-tbl-0001:** EPIC‐VT protocol.

	Inclusion visit		Randomization	D‐1		Radiofrequency Ablation	Before hospital discharge		6‐month follow‐up phone call^a^ (M6 ± 1 month)		12‐Month consultation (M12 ± 1 month)		18‐month follow‐up phone call^a^ (M18 ± 1 month)		24‐Month consultation (M24 ± 1 month)		Data collection post 24 months	
Actions	CP	AR		CP	AR		CP	AR	CP	AR	CP	AR	CP	AR	CP	AR	CP	AR
Information and Consent		X																
Verification of Selection Criteria		X																
Pregnancy Test		X																
Verification of Medical History	X																	
Standard Preoperative Biological Assessment				X														
Echocardiography							X											
Clinical Examination	X			X			X											
ICD Interrogation							X											
Medications Taken	X			X			X			X		X		X		X		
Imaging (Exclusion of Thrombus)				X^b^														
Inquiry About Adverse Events							X			X								
Remote monitoring (VT/VF episodes)										X		X		X		X		X

Abbreviations: CP = clinical practices, AD = added by the Research.

^a^
or during a scheduled consultation;

^b^
From 1 Month to 1 Day Before.

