#### Secondary Outcome

2.6.2

The secondary outcomes are: (i) the number of ventricular arrhythmias requiring ICD treatment or hospitalization; (ii) the percentage of patients with ventricular arrhythmia recurrence at 2 years; (iii) the percentage of patients experiencing an electrical storm at 2 years, defined as the occurrence of at least three appropriate therapies (ATP or shocks) delivered by the ICD within 24 h; (iv) the rate of serious complications related to the procedure at 1 month; (v) procedure duration (from puncture to catheter removal, in minutes) and radiofrequency duration (in minutes); (vi) the number of patients hospitalized for cardiovascular reasons (e.g., heart failure, arrhythmias) at 2 years; (vii) the number of patients requiring a repeat ablation; (viii) the mortality rate at 2 years; (ix) the number of patients with non‐inducibility at the end of the procedure; (x) the percentage of patients who experienced inappropriate therapy at 2 years; (x) the duration of hospitalization postablation (days from ablation to hospital discharge) to assess post‐procedural recovery.

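### The one complication outcome need not count thromboembolic events during the pre-procedure antithrombotic interruption, which the plan makes much longer in the endo-epicardial arm

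*Protocol article*

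**What the plan says.** Section 2.6.2 of the protocol article lists one outcome that counts complications, item (iv): "the rate of serious complications related to the procedure at 1 month". Two other secondary outcomes bear on harm and have no relatedness condition: "the number of patients hospitalized for cardiovascular reasons" at 2 years (vi) and "the mortality rate at 2 years" (viii).

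Section 2.2 makes the handling of blood thinners part of the allocation: "Antithrombotic treatment will be adapted according to the randomization group". In the endocardial arm (section 2.3.2), a morning DOAC dose or "the evening dose (evening dose of rivaroxaban) will be withheld"; VKA patients proceed at an INR below 3; and for antiplatelets "the procedure will be performed regardless of the combination of antiplatelet therapy". In the endo-epicardial arm (section 2.3.3), DOACs stop 3 or 4 days ahead, "for patients on VKAs, therapy will be discontinued 5 days before the procedure" with an INR below 1.5 required, and aspirin is the only antiplatelet continued, the others stopping at least 5 days ahead.

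Table 1 marks the row "Inquiry About Adverse Events" before discharge and at the 6-month call, not at the D-1 contact. Section 2.7.2 defines a modified intention-to-treat population of patients randomised and undergoing ablation.

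**The concern.** The trial compares two first-line strategies, and in each the strategy starts when the antithrombotic drugs are adapted, not at the puncture. A stroke, systemic embolism, stent thrombosis or infarction while drugs are withheld is a possible harm of the assigned strategy. The exposure lies mainly in the endo-epicardial arm.

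A complication outcome tied to the procedure, in patients who reach it, can miss such an event. Any loss would fall mainly on the experimental arm and make it look safer. This matters because the abstract foresees the combined approach becoming the preferred option, while the Discussion's own meta-analytic figure leaves harm unresolved: a complication ratio of 1.88 with a 95% CI of 0.19 to 18.76.

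**Working it through.** The plan gives no expected rate or precision for outcome (iv), so there is no figure to reproduce. The check sets the sections side by side and then gives a sense of scale.

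**Step 1. Exposure by arm (sections 2.3.2 and 2.3.3).**

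| Drug class | Endocardial only | Endo-epicardial |
|---|---|---|
| DOAC | one dose held | last dose at least 3 days before (apixaban, rivaroxaban) or 4 days (dabigatran) |
| VKA | no stop stated; INR < 3 the day before | stopped 5 days before; INR < 1.5 the day before |
| Antiplatelets | any combination accepted | aspirin alone; others stopped at least 5 days before |

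The difference is several days in every class, and it arises after randomisation.

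**Step 2. When the clocks start.** Section 2.1 counts participation from the ablation date, section 2.6.1 starts the primary endpoint there, and section 2.4 times contacts from the procedure. Nothing in section 2.6.2 starts any secondary outcome at randomisation.

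**Step 3. Three patients followed through the plan.**

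- *Stroke during interruption, ablated later.* It precedes the procedure. It enters (iv) only if relatedness covers preparation and the window opens before ablation. It enters (vi) only if the 2-year clock also opens before ablation.
- *Stroke during interruption, never ablated.* If section 2.7.2 is read as analysing only those who undergo ablation, this patient leaves every comparison. The following sentence there limits exclusions to persistent thrombus, which would keep the patient in. But there is then no ablation date from which the month can run.
- *Infarction days after ablation.* It enters (iv) only if judged related. If it leads to a cardiovascular admission it should appear in (vi), and if fatal in (viii).

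**Step 4. Data capture.** Table 1 has no adverse-event enquiry until discharge. That enquiry can look back in patients who were ablated, but not in those who never were.

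**Step 5. Scale (illustration only).** The documents give neither the share of patients on these drugs nor the event risk. Inputs:

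- Patients per arm: 150 / 2 = 75 (section 2.7.1, 1:1 allocation).
- Share of endo-epicardial patients interrupted: 30% to 70% (assumed).
- Serious thrombotic event risk among them: 0.2% to 2% (assumed).

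Uncounted events = 75 × share × risk:

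- Low: 75 × 0.30 × 0.002 = 0.045, or 0.06 percentage points.
- High: 75 × 0.70 × 0.02 = 1.05, or 1.4 percentage points.

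For comparison, the 3.6% complication risk that the Discussion cites for epicardial ablation in experienced centres gives 75 × 0.036 = 2.7 events. One uncounted event would be 1 / 2.7 = 37% of that. The 3.6% comes from a cited report, not from this trial's outcome definition.

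**The case against.** The strongest reply is that the plan already covers much of this. Mortality and cardiovascular hospitalisation at 2 years carry no relatedness filter, and most infarctions and stent thromboses, and probably most strokes, would lead to admission. Patients whose anticoagulant cannot be paused, or whose dual antiplatelet therapy cannot be reduced to a single agent, are excluded (section 2.2). Aspirin continues, and imaging must rule out ventricular thrombus. The article leaves relatedness undefined; the full protocol may define it, and mandated preparation can be read as part of the procedure. Procedural harm is also where the epicardial arm is expected to do worse, so replacing (iv) with all serious events could blur that contrast at 75 per arm.

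Much of this stands, and it rules out several stronger readings that a reader might infer:

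- *That (iv) is the only safety outcome.* It is the only complication outcome; (vi) and (viii) also bear on harm.
- *That interruption harms are excluded.* The text neither includes nor excludes them.
- *That an unblinded investigator judges relatedness.* The trial is open-label, but the article does not say who judges.
- *That adverse events collected at 6 months are discarded.* That call is the first scheduled contact after discharge, so it is a natural source for the 1-month outcome.

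What the reply does not remove is the gap between randomisation and ablation. Outcomes (vi) and (viii) are not clearly counted from randomisation, they mix in heart failure and arrhythmia events, and a patient never ablated may be outside the analysis set. The exclusions reduce the risk in those enrolled but do not cause events to be counted.

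**Conclusion.** The concern holds in a limited form. Followed as written, the plan need not count thromboembolic events that arise during an interruption it assigns mainly to one arm, or that occur in patients who are then not ablated. The complication comparison may therefore favour the endo-epicardial arm. It cannot be said that it does: that depends on how relatedness and the start of the window are defined, and it concerns only patients taking these drugs.

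The size cannot be derived from the documents. Under the assumptions in the working it runs from about 0.05 to 1.05 events in 75 patients. That is small in absolute terms, but the upper end is not negligible beside an expected count of a few complications. A reader might suppose one or two missed events; nothing in the documents supports that, and two would lie above the illustrative range. The primary endpoint analysis is not affected by this point.

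**What to change.** Keep procedure-related serious complications at 1 month as an outcome in their own right. Add a second safety outcome: all serious adverse events from randomisation to 1 month after ablation (or after the planned ablation date if none takes place), regardless of attribution, in all randomised patients by allocated arm. Show thromboembolic or ischaemic, bleeding and pericardial events separately. Add an adverse-event enquiry at the existing D-1 contact in Table 1.

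The cost is outcome and analysis wording, one question at a contact that already takes place, and a check on the few patients not ablated, for whom no post-procedure contact occurs. The discharge and 6-month enquiries and the hospital reports under section 2.4 supply the rest. The drawback is noise from unrelated events in a population prone to admissions, which is why the procedure-related outcome stays separate. No change to antithrombotic management is proposed.

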### Sample Size and Statistical Considerations

2.7

#### Sample Size Estimation

2.7.1

In two meta‐analyses investigating ICM patients outcomes after endo‐epicardial ablation, the risk of ventricular arrhythmia recurrence at 2 years was 50% in the ‘endocardial‐only’ group and 26% in the ‘endo‐epicardial’ group (HR = 0.43) [20, 21]. To demonstrate this difference, it is necessary to observe 59 events to ensure 90% power with a two‐sided α risk of 5%. To observe a minimum of 59 events required for analysis, we planned to evaluate 150 patients followed for a period of at least 2 years. After the 2‐year follow‐up, patients will no longer be monitored as part of the study, but the ICDs will be remotely interrogated via telemonitoring for patients with no recurrence until (i) arrhythmia recurrence or at the latest (ii) the date of the last visit of the last patient included.

Of note, the sample size estimation is based on treatment effect derived from a prior meta‐analysis of observational studies. However, we acknowledge that the endocardial ablation strategies varied significantly across the included studies, ranging from targeted ablation of clinical/induced VT to complete scar homogenization. This heterogeneity may have influenced the estimated benefit of a combined endo‐epicardial approach and represents a limitation of the current power calculation.

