### Follow‐Up Visit

2.4

The patient will receive a telephone call at 6 and 18 months, and will be seen in a consultation at 1 and 2 years following the procedure. This will allow the medical team to inquire about any hospitalizations and the use of antiarrhythmic medications. Remote monitoring will be used to retrieve any recorded arrhythmic event. In the event of hospitalization or consultation, the center or healthcare professional who manages the patient will be contacted to obtain hospitalization reports and check for the occurrence of ventricular arrhythmia.

After 2 years of follow‐up, patients included in the study with a successful procedure and no recurrence will be followed up remotely until (i) arrhythmia recurrence or at the latest, or (ii) the date of the last visit of the last patient included.

Of note, if a new ablation is required during follow‐up due to arrhythmia recurrence, the choice of approach (endocardial only or combined endo‐epicardial approach) will be left to the discretion of the medical team in charge of the patient.

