#### Primary Outcome

2.6.1

The primary endpoint is survival without ventricular arrhythmia recurrence, defined as the interval between the date of ablation and the date of the first recurrence of ventricular arrhythmia. Ventricular arrhythmia recurrence will be defined as the occurrence of an appropriate therapy delivered by the ICD or the occurrence of sustained VT/VF lasting more than 30 s requiring hospitalization. The occurrence and date of the event will be obtained from ICD interrogation. Patients without recurrence will be censored on the date of the last ICD interrogation.

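### After month 24 the primary analysis continues on remote ICD data alone, so no planned step establishes VT/VF requiring hospitalization, one of the two components of the primary event

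*Protocol article*

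**What the plan says.** Four places in the protocol article bear on this.

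- **Section 2.6.1 (Primary Outcome)** defines recurrence as "the occurrence of an appropriate therapy delivered by the ICD or the occurrence of sustained VT/VF lasting more than 30 s requiring hospitalization". On source it says "The occurrence and date of the event will be obtained from ICD interrogation", with no time limit. On censoring it says "Patients without recurrence will be censored on the date of the last ICD interrogation".
- **Section 2.4 (Follow-Up Visit)** sets the contacts: "The patient will receive a telephone call at 6 and 18 months, and will be seen in a consultation at 1 and 2 years" after the procedure. Hospitalizations are asked about at these contacts. Where there was one, the treating centre or professional "will be contacted to obtain hospitalization reports and check for the occurrence of ventricular arrhythmia". After 2 years, follow-up is remote, until recurrence or the last visit of the last patient.
- **Section 2.7.1 (Sample Size Estimation)** describes the later period: "patients will no longer be monitored as part of the study, but the ICDs will be remotely interrogated via telemonitoring" for patients with no recurrence, with the same end point.
- **Table 1 (Section 2.5.1)** marks a single row in its post-24-month column, the remote monitoring of VT/VF episodes.

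Section 2.7.2 then applies one log-rank test to the primary endpoint, with no limit on follow-up time.

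**The concern.** The second component of the primary event has two parts: a sustained arrhythmia, and its having required hospitalization. An ICD log can date an episode but cannot show that the patient was admitted for it. Under the programming in Section 2.3.4, VT in a monitor zone would be recorded without therapy, and VT slower than the lowest programmed zone may not be recorded at all. Up to month 24, the inquiry and report retrieval in Section 2.4 close that gap. After month 24 no planned step does.

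A patient admitted in the third year for VT that the device did not treat could therefore stay in the risk set as recurrence-free until the last interrogation. Some events would be lost or dated late, and the arrhythmia-free curves beyond 2 years would rest on less complete ascertainment than the part before. That matters because the Discussion states the aim as improving long-term arrhythmia-free survival.

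**Working it through.** **1. The plan's own figure.** Schoenfeld's formula with 1:1 allocation, two-sided 5%, 90% power and HR 0.43:

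events = 4 × (1.960 + 1.282)² / (ln 0.43)² = 59.0

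This reproduces the stated 59.

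**2. Does the plan need time after month 24?** With 75 patients per arm and the stated 2-year risks of 50% and 26%:

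75 × 0.50 + 75 × 0.26 = 37.5 + 19.5 = 57 events by month 24

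Power = Φ(|ln 0.43| × √57 / 2 − 1.960) = 0.890. With 3% of patients excluded, 0.97 × 57 = 55.3 events and power is 0.881. The plan therefore relies on some later follow-up to reach 59.

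**3. Events expected after month 24.** Assumptions: exponential hazards, λ₀ = ln 2/24 and λ₁ = −ln(0.74)/24 per month; uniform accrual over R months; last patient followed for 24 months; no dropout or death. Expected events per arm are

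75 × [1 − (e^(−24λ) − e^(−(24+R)λ)) / (λR)]

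The accrual length is an assumption. Section 2.1 gives recruitment dates spanning 60 months and also a 60-month total duration, which with 24 months of follow-up would leave 36 months for accrual. A 12-month value is added as a low case.

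| Accrual | Endocardial | Endo-epicardial | Total | After month 24 |
|---|---|---|---|---|
| 12 months | 43.3 | 23.5 | 66.8 | 9.8 (15%) |
| 36 months | 51.7 | 30.3 | 82.0 | 25.0 (31%) |
| 60 months | 57.2 | 36.0 | 93.2 | 36.2 (39%) |

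**4. Events that could be missed.** The protocol gives no share for hospital-only events. For an assumed 5% to 20%, power at HR 0.43 is:

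| Accrual | Missed at 5% | Missed at 20% | Power, none missed | Power, 5% to 20% missed |
|---|---|---|---|---|
| 12 months | 0.5 | 2.0 | 0.932 | 0.930 to 0.925 |
| 36 months | 1.3 | 5.0 | 0.969 | 0.967 to 0.959 |
| 60 months | 1.8 | 7.2 | 0.983 | 0.981 to 0.975 |

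For a given share these losses are upper figures, because a patient whose admission is missed may later receive appropriate therapy and be counted at that later date.

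**5. Effect on the curves.** If the observed hazard after month 24 is (1 − s) times the true one in both arms, the arrhythmia-free proportion at month 60 is 0.50 × e^(−36λ₀(1−s)) for endocardial and 0.74 × e^(−36λ₁(1−s)) for endo-epicardial.

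| Share missed (s) | Endocardial | Endo-epicardial | Difference |
|---|---|---|---|
| 0 | 17.7% | 47.1% | 29.4 points |
| 5% | 18.6% | 48.2% | 29.6 points |
| 20% | 21.8% | 51.6% | 29.8 points |

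Under these assumptions each curve is too high by about 1 to 4.5 points at month 60, while the difference between arms moves by less than half a point.

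**The case against.** The strongest reply is that Section 2.6.1 names ICD interrogation as the source of the event throughout, so nothing switches at month 24. The report-retrieval sentence in Section 2.4 carries no end date, and Table 1 has no hospitalization row at any time, so its silence after month 24 proves little by itself. This stands in part: the stop at month 24 is read from the contact schedule and from the statement in Section 2.7.1 that study monitoring ends, and is not announced as a change of source. But the literal reading of Section 2.6.1 does not rescue the endpoint. It would leave the hospitalization criterion without a source at any time. On either reading the sections need reconciling.

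It can also be said that few events are at risk. All patients have a telemonitored ICD, and the VT zone is set below the clinical VT rate where that is known, so most recurrences should be captured as therapy. That is fair, and it is why the 5–20% share is only an assumption.

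Three stronger readings are tempting, and the document does not support them.

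- **The event definition narrows after month 24.** The written definition is unchanged; only its ascertainment differs.
- **The late hazard is too low by construction.** The direction is not certain. Remote monitoring retrieves episodes as well as therapies, and Section 2.4 follows patients until arrhythmia recurrence without restating the criteria. If any logged VT were counted, the effective event would widen.
- **The treatment comparison is biased because more of the endo-epicardial arm's time at risk lies after month 24.** The change falls at the same time since ablation in both arms, and the log-rank test compares patients at equal times, so it is not in itself differential.

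Finally, no absolute risk beyond 2 years is a specified outcome, and Section 2.6.2 already lists recurrence at 2 years. That limits the harm, but the late follow-up still enters the primary test and any curve drawn from it.

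**Conclusion.** The point holds as a gap in ascertainment. Follow-up after month 24 counts in the primary log-rank test, and the procedure stated for that period cannot establish hospitalization. Because the article states that procedure, this is not a detail left to a fuller document.

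The size is modest. With 36 or 60 months of accrual, about 31% or 39% of expected events fall in the affected period, and roughly 1 to 7 could be missed if 5–20% of events are hospital-only. Power stays above 90% and drops by at most about 1 point. If the loss is proportional in both arms, the hazard ratio is little changed. What is mainly exposed is the level of the arrhythmia-free curves beyond 2 years. All of this rests on the protocol's 2-year risks, exponential hazards, no dropout, and assumed accrual and hospital-only shares. The point merits correction because the remedy is cheap.

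**What to change.** Reconcile Sections 2.4, 2.6.1, 2.7.1 and Table 1 so that one source and one rule for both components of the primary event cover the whole analysed period.

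- **Add a closing check.** In the post-24-month column of Table 1, add one hospitalization inquiry, with report retrieval as in Section 2.4, for each recurrence-free patient at the last visit of the last patient. State in Section 2.6.1 that device data and hospital reports together establish the event, and that a logged episode meeting neither component does not count.
- **Settle who is covered.** Section 2.4 limits later follow-up to patients with a successful procedure and no recurrence, whereas Section 2.7.1 requires only no recurrence. The same edit should align them.
- **Add two sensitivity analyses.** Report the log-rank test and Kaplan–Meier curves censored at 24 months, and a version using ICD therapy alone throughout. The 24-month version should not replace the primary analysis, since 57 events are expected by then against 59 required.

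The cost is protocol wording and one extra telephone or records contact per recurrence-free patient. The sensitivity analyses use data already collected, and the 59-event calculation is unchanged.
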